### Sample Size

In this pilot study, the sample size was estimated according to the grade (Gr) of the Radiation Therapy Oncology Group (RTOG) (Cox et al., 1995) and National Cancer Institute (NCI) (Trotti et al., 2000) for the RID reported in the relevant literature. Kong et al. (Kong et al., 2016) investigated the incidence rate of RTOG Gr ≥ 2 in breast cancer patients with RID using Jaungo, which is the primary outcome in this study, at 46.7%. For non-steroidal moisturizer, there was no primary report using RTOG grade, but the incidence rate of NCI Gr ≥ 2 of RID in breast cancer patients was 9.0% (Leonardi et al., 2008). Clinically, the RTOG and NCI are common assessment grading tools, and each value of the incidence rate is compatible. Therefore, we estimated the incidence rates of the Jaungo and the moisturizer groups to be 0.467 and 0.09, respectively. The formula for calculating the sample size is as follows:$$n_{c}=\;\frac{\left(1+\lambda \right)\sigma^{2}{\left(Z_{\alpha /2}+Z_{\beta }\right)}^{2}}{\lambda d^{2}}$$

At the 5% significance level, considering an estimated withdrawal rate of 15%, a total of 50 participants, 25 in each group will be required to achieve 80% power.

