### Outcome Measurement

The participants will be assessed at every visit during RT and 2 weeks after the end of RT. The assessment will be conducted by radiation oncologists who do not know which group the participant belongs to, and will be single-blinded. The date of the occurrence and severity of RID will be evaluated at every visit from the start to end of RT and 2 weeks after, based on the RTOG grade. An incidence rate of Gr ≥ 2 RID will be recorded as the primary outcome of this study. At the start and end of RT and 2 weeks later, the quality of life (QOL), skin reaction symptoms, and maximum pain related to RID will be measured based on the Catterall skin scoring profile (CSSP) (Catterall et al., 1971), the Korean version of Skindex-29 (Ahn et al., 2004), and numeric rating scale (NRS) (Haefeli and Elfering, 2006). The maximum grade of RID, time to onset of RID, the value of CSSP, the Korean version of Skindex-29, and NRS, and the types and frequencies of adverse events will be compared as secondary outcomes between the two groups.

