#### Catterall Skin Scoring Profile

The CSSP was developed by Fowler to allow the evaluation of skin reaction in mice, and was later modified by Catterall in 1965 to apply a numeric scale-type assessment tool (Catterall et al., 1971). It is classified as 1–10 points, depending on the symptoms and severity of dermatitis: 1, no visible reaction; 2, light erythema; 3, moderate erythema; 4, severe erythema; 5, dry desquamation <50% of irradiated are; 6, dry desquamation >50% of irradiated area; 7, blistering present; 8, moist desquamation <50% of the irradiated area; 9, moist desquamation >50% of the irradiated area; 10, ulceration present.

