#### Skindex-29

Skindex-29 is a revision of the existing 61 questions of Skindex to 29 questions for patients with skin diseases. Skindex-29 is a QOL assessment tool designed to evaluate the QOL of a patient on three scales of symptoms, function, and emotion, while maintaining excellent reproducibility, reliability, recruitment validity, and content validity of Skindex. In this study, we will use the Korean version of Skindex-29 published by Ahn et al. (2004), which is a 5-level Likert scale from 1 (never) to 5 (always) and has been validated.

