#### Numeric Rating Scale

NRS is a pain evaluation tool that uses the visual pain score (Haefeli and Elfering, 2006). NRS 0 is defined as the state without discomfort, and NRS 10 is the maximum degree of discomfort that the patient can think of.

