### Statistical Analysis

The collected data will be statistically assessed using SPSS Version 25.0 (Chicago, IL), based on the intention-to-treat (ITT) set, except for the following subjects: 1) subjects who violate the inclusion/exclusion criteria; 2) subjects who have never used the intervention medication; and 3) subjects who have not provided any data after screening. The demographic characteristics of all participants will be reported as the mean and 95% confidence interval (95% CI) for continuous variables or frequencies and percentages for categorical variables. The incidence rate of RTOG Gr ≥ 2 RID, the primary outcome of this study, will be evaluated the difference between two groups using the Chi-squared test. Among the secondary outcomes, the maximum grade of RID based on RTOG will be analyzed by Chi-squared test, the time to RID occurrence by Kaplan-Meier analysis, and the CSSP, Skindex-29, and the maximum NRS for RID-related pain by independent sample t-test or Mann-Whitney U test, depending on the normal distribution, to compare the differences between the two groups. Adverse events will be presented as descriptive statistics by dividing according to the severity of each intervention and adverse symptoms. The types and frequencies of adverse events determined to be causative of the intervention will be separately analyzed and reported. Differences will be considered statistically significant when *p* < 0.05. Adverse reactions will be presented as descriptive statistics, divided according to the severity of each group and each adverse event. The symptoms and frequencies of adverse reactions related to the intervention medication will be analyzed separately.

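### Skindex-29 is measured at the start of RT, but the stated test names no use of that value; a baseline-adjusted analysis costs about 2% of variance at worst and may gain much more, and each scale's test should be fixed in advance

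*Protocol article*

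**What the plan says.** Under Outcome Measurement, the protocol article sets three measurement times for the patient-level scores: "At the start and end of RT and 2 weeks later, the quality of life (QOL), skin reaction symptoms, and maximum pain" are assessed with CSSP, Skindex-29 and NRS. The same section makes them secondary: "the value of CSSP, the Korean version of Skindex-29, and NRS, and the types and frequencies of adverse events will be compared as secondary outcomes".

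Statistical Analysis compares CSSP, Skindex-29 and the maximum NRS for RID-related pain by "independent sample t-test or Mann-Whitney U test, depending on the normal distribution". It names no covariate, change score or analysis time point for these scores. The only confidence interval it mentions is for describing demographic variables.

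Three descriptions of the instruments matter here:
- Skindex-29 is designed to "evaluate the QOL of a patient on three scales of symptoms, function, and emotion".
- For CSSP: "It is classified as 1–10 points, depending on the symptoms and severity of dermatitis: 1, no visible reaction".
- For pain: "NRS 0 is defined as the state without discomfort".

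**The concern.** Two separate matters sit in one sentence of the analysis plan.

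The first is the unused start value. Skindex-29 covers symptoms, function and emotion in women who have recently had breast surgery. Their scores plausibly differ before the first fraction, and patients who score high then may score high later. A two-sample test on follow-up values leaves that variation in the error term. With 25 per arm the difference is estimated imprecisely anyway, so a covariate that is already collected is worth using.

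The second is the choice of test. A t-test compares means and Mann-Whitney compares ranks. If the data decide between them, the quantity reported is not known in advance, and it can differ between scales or between the two follow-up times of one scale.

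**Working it through.** **The plan's own figure.** Sample Size states "we estimated the incidence rates of the Jaungo and the moisturizer groups to be 0.467 and 0.09, respectively", and "At the 5% significance level, considering an estimated withdrawal rate of 15"%, with 80% power and 25 per group. The usual two-proportion formula without continuity correction gives:

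n = [1.960·√(2·0.2785·0.7215) + 0.842·√(0.467·0.533 + 0.09·0.91)]² / 0.377² = (1.242 + 0.484)² / 0.1421 ≈ 21 per arm.

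Then 21/0.85 = 24.7, so 25 per arm and 50 in total. The stated size reproduces. It rests on the binary primary outcome alone, so nothing below changes it.

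**Precision from the start value.** Inputs: n = 25 per arm (or 21 after 15% withdrawal), 1:1 allocation, and a baseline-to-follow-up correlation r. The document does not give r, so r = 0 to 0.7 is an assumption. Relative to the unadjusted follow-up comparison:

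- ANCOVA variance ratio, VR = (1 − r²)·(2n − 3)/(2n − 4). The second factor is the cost of estimating the slope: 47/46 = 1.022 at n = 25 and 39/38 = 1.026 at n = 21.
- Raw change score, equal SDs: 2 − 2r.
- Power at a standardised difference of 0.5 (normal approximation): Φ(0.5·√(n/(2·VR)) − 1.96). Unadjusted power is 42% at n = 25 and 37% at n = 21.

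| r | VR, n = 25 | Effective n per arm | Power, n = 25 | VR, n = 21 | Power, n = 21 | Change-score ratio |
|---|---|---|---|---|---|---|
| 0 | 1.02 | 24.5 | 42% | 1.03 | 36% | 2.0 |
| 0.3 | 0.93 | 26.9 | 45% | 0.93 | 39% | 1.4 |
| 0.5 | 0.77 | 32.6 | 52% | 0.77 | 46% | 1.0 |
| 0.7 | 0.52 | 48.0 | 69% | 0.52 | 61% | 0.6 |

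The worst case for adjustment is a variance 2 to 3% larger. At r = 0.5 the variance falls by 23%.

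**Chance imbalance.** The SD of the difference in baseline means is √(2/25) = 0.28 SD. An imbalance beyond 0.3 SD in either direction has z = 0.3/0.283 = 1.06, a probability of about 29%. With equal SDs the unadjusted difference shifts by r times the imbalance: 0.5 × 0.3 = 0.15 SD at r = 0.5, and nothing at r = 0.

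**Which scales this reaches.** CSSP and NRS have floors at 1 (no visible reaction) and 0 (no discomfort). Before radiation there should be almost no radiation reaction or RID-related pain, so these start values should be nearly constant and carry little information. Skindex-29 is the scale for which a useful r is plausible.

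**The normality gate.** A simulation (4,000 runs per scenario) used the t-test if both arms passed a Shapiro-Wilk test at 5%, and Mann-Whitney otherwise. At 25 per arm and a standardised difference of 0.8:

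| Data | t-test | Mann-Whitney | Gated rule |
|---|---|---|---|
| Normal | 80% | 78% | 80% |
| Lognormal | 82% | 98% | 98% |

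Type I error of the gated rule was 4.4 to 5.4% over 21 and 25 per arm, within simulation error of 5%. So the gate costs neither power nor error control. It does make the estimand random: with truly normal data, about 10% of comparisons still failed the check and switched to ranks. If three Skindex-29 scales, CSSP and NRS are each tested at two follow-up times, there are 5 × 2 = 10 such decisions.

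**The case against.** The strongest reply is that the article condenses a fuller plan. It does not say that follow-up values rather than changes are compared, and covariates and time points may be set elsewhere. It is fair that non-use of the start value is inferred from the tests named. But the method itself is stated, and the silence does not rescue it. Raw change is less precise than follow-up values when r is below 0.5, and ANCOVA is at least as precise as either reading apart from the cost of about 2%.

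Three stronger readings are tempting, and the documents do not support them:
- **That all three scales lose precision.** Post-operative pain might vary before RT, but the outcome is pain related to RID, and Exclusion Criteria rule out an unhealed breast scar. For NRS and CSSP the gain should be close to nil.
- **That choosing the test by normality wastes precision.** The simulation shows no loss.
- **That a baseline imbalance passes in full into the group difference.** It carries over only in proportion to the baseline-to-follow-up slope, and the unadjusted comparison remains valid under randomisation.

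It is also true that low correlations are plausible, because the toxicity arises after the start value is taken. At r = 0.2 the gain at 25 per arm is only about 2% (0.96 × 1.022 = 0.98). A large gain is possible, not established.

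**Conclusion.** The point holds for Skindex-29 as a matter of efficiency, not of bias. The stated analysis names no use of a start value that the trial collects. At 25 per arm, adjustment changes the variance by a factor between 1.02 and 0.52 over assumed correlations of 0 to 0.7; it becomes material at about 0.5 and above. The text of the plan is clear. The size of the gain is uncertain, because the document gives no SD, correlation or baseline distribution, and the floor values of CSSP and NRS before RT are also assumed.

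The normality condition is a separate and smaller fault of pre-specification: whether means or ranks are compared should not depend on the data. Both matters concern secondary outcomes of a pilot. The change is worth making, but no primary conclusion depends on it.

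**What to change.** Rewrite the sentence on these scores in Statistical Analysis:

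- **Skindex-29, each of the three scales:** ANCOVA of the end-of-RT value, and separately of the 2-week value, on group and the start-of-RT value. Report the adjusted mean difference with its 95% CI.
- **CSSP and RID-related NRS:** one rank-based test, Mann-Whitney, named in advance together with the time points at which it is applied.
- **All scales:** delete the clause that lets normality decide the test.

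The cost is a rewritten sentence. The start values are already scheduled, SPSS fits the model directly, and no visit, patient or measurement is added.

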## Discussion

This is a prospective, single-blinded, pilot randomized-controlled trial to compare the preventive efficacy of Jaungo ointment and the water-in-oil type non-steroidal moisturizer for RID in patients with breast cancer undergoing RT after surgery. The number of participants was conducted for a total of 50 subjects, 25 in each group, based on prior studies. One of the two topical agents (Jaungo or moisturizer) will be randomly applied to the irradiated lesion from the start to the end of RT. In this protocol, the incidence and severity of RID and RT-related skin reactions, QOL, and pain based on RTOG, CSSP, the Korean version of Skindex-29, and NRS will be measured. The primary outcome will be the incidence rate of RID of Gr ≥ 2 based on the RTOG. All assessments will be conducted by independent radiation oncologists, blinded to the group.

RT is a widely applied conventional therapy for patients with cancer. Indeed, at least 50% of patients with any type of cancer receive RT during their treatment, and this prevalence is higher in patients with breast cancer up to 70% (Baskar et al., 2012). Almost 95% of patients receiving RT experience RID during or after the course of therapy, and 25% develop severe skin reactions (Iacovelli et al., 2020). The pathogenesis of RID is associated with radiation-induced vascular damage, followed by leukocyte infiltration and destruction of the skin barrier, resulting in inflammation and vasculitis (Weintraub et al., 2010). Patients may experience a variety of symptoms, such as pruritus, erythema, edema, desquamation, necrosis, ulceration, and hemorrhage. Furthermore, one out of three patients with breast cancer develop chronic RID, which can appear up to 10 years after the completion of RT. As such, RID is one of the most widespread side effects of conventional cancer therapies and has major consequences on QOL and adherence to RT course and dosage of irradiation, thereby even discontinuing RT and adversely affecting clinical outcomes (Leventhal and Young, 2017).

The risk of developing RID in breast cancer is dependent on various factors. Therapy-related factors include radiation dose, duration of irradiation, volume of the breast, and combination with other conventional therapies. The incidence of RID is also influenced by patient-related factors, such as high body mass index, nutritional status, smoking, alcohol, pre-existing skin disease, and genetic susceptibility (Böhner et al., 2020). As such, RID can be caused by a variety of factors and accounts for a high proportion of the adverse effects of conventional therapies in breast cancer patients, but there is currently no standard management or guideline for RID prevention (Wong et al., 2013; Chan et al., 2014). However, in clinical practice, topical managements, including moisturizing cream, are generally applied to patients with RID and their comparative studies have also been researched (Haruna et al., 2017; Ahn et al., 2020).

The water-in-oil type non-moisturizer cream, which consists of hyaluronic acid, shea butter, glycyrrhetinic acid, vitis vinifera, and telmesteine, was registered as a medical device for the symptomatic treatment of RID in the United States (US) and European Union (EU) (Primavera et al., 2006). Its components are believed to minimize radiation-induced skin reactions. All ingredients are powerful moisturizing agents that can attract and retain water under the skin barrier. In particular, hyaluronic acid, the main ingredient of the non-steroidal moisturizer, has demonstrated remarkable hygroscopic properties that are relevant to wound healing (Abramovits and Boguniewicz, 2006). Additionally, glycyrrhetinic acid has been reported to accumulate endogenous hydrocortisone and act as a natural steroid with anti-inflammatory properties (Kroes et al., 1997). Given the mechanism of these ingredients, the water-in-oil type non-moisturizer cream has shown significant efficacy at treating maximum severity skin toxicity, the severity of erythema, burning sensation within the radiation lesion, and desquamation, when compared to emollient base cream, which is similar in color and consistency to the moisturizer, but without the key ingredients (Leonardi et al., 2008). Therefore, it has been regarded as one of the available treatment regimens effective in the prevention of RID and the promotion of relief RT-related skin reactions.

Jaungo, a traditional herbal ointment consisting of *Lithospermi radix* and *Angelica sinensis*, is standardized based on the Korean Pharmacopeia. It has been authorized as a topical drug for dermatitis by the Korea Food and Drug Safety Administration (KFDA). In clinical practice, Jaungo has been used to treat a variety of dermatopathy symptoms, including RID. A few clinical trials have demonstrated the preventive effects of Jaungo on RID. A recent study found that Jaungo reduced the incidence of Gr ≥ 2 (46.7 versus 78.6%) and Gr 3 RID (20.0 versus 50.0%) without adverse events compared to general supportive skincare including gentle washing with neutral pH soap instead of prophylactic lotions or moisturizers, although it was not statistically significant (Kong et al., 2016). Additionally, brain tumor patients who underwent RT showed significant prevention of scalp dermatitis after topical application of Jaungo (Hayashi and Sato, 2011). In particular, shikonin, acetylshikonin, ferulic acid, and decusin, the major components of *Lithospermia radix* and *Angelica sinensis*, have been reported to have wound healing, antibacterial and anti-inflammatory effects (Huang et al., 2004; Hsiao et al., 2012; Ghaisas et al., 2014).

Given this background, we evaluated the comparative efficacy of Jaungo and the non-steroidal moisturizer in the prevention of RID in postoperative breast cancer patients. To our knowledge, this study is the first randomized controlled trial comparing topical agents to investigate the prophylactic efficacy between Jaungo ointment and the water-in-oil type non-steroidal moisturizer, which is one of the major clinical topical managements of RID for breast cancer patients with RID. This study can be considered as a noteworthy study protocol for highly prevalent RID without standard treatment, despite the limitations that double-blindness cannot be achieved, a pilot study with a small sample size, and the evaluation of outcomes may be subjective, depending on the assessors.
